### Statistical analysis

3.5

The analysis will be performed using the Stata IC 15 program.

-Specific objective 1. We will calculate the proportion of false positive and false negative results for the diagnosis of PCa and the associated variables. In the case of false positive tests, we will also describe the time from a positive PSA result until PCa is ruled out using mean, standard deviation or median and interquartile ranges for the total population and relevant subgroups. In order to analyze clinical and analytical factors associated with the presence of false positive and false negative results in PSA determinations, we will calculate prevalence ratios and their 95% confidence interval with log-binomial regression.-Specific objective 2. We will assess the probability of having a diagnostic, surgical or therapeutic intervention according to variables using risk ratios with their 95% confidence intervals. If necessary, we will adjust for potential confounders using log-binomial regression. We will also evaluate the agreement between the interventions performed and the available guidelines.^[20]^ We will evaluate the inter-observer agreement in the determination of appropriateness using the Kappa index.

Steps will be taken to prevent missing data (e.g., we will periodically review medical records and access data from different sources such as records of primary, specialized and hospital care), but some level is unavoidable and we will incorporate methods analyzing missing data or data from uncertain sources when necessary.^[33,34]^

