#### Sample size and recruitment procedure

3.2.2

According to a review by the American Cancer Society,^[31]^ a value of PSA of 4 μg/L had an estimated sensitivity of 21% to detect any type of prostate cancer and a specificity of 91%. We estimate a prevalence of PCa in this population not lower than 5% (given that we include asymptomatic and symptomatic patients), with a 95% margin of error and 2% precision, we will need to include 457 patients with a negative PSA result and 865 PSA-positive patients. Taking into account a 20% possible loss during follow-up, we will increase to 572 patients with a negative PSA result (286 per center) and 1081 patients with a positive PSA result (541 per center) who will be selected consecutively from among those included in the previous cross-sectional study (NCT03968692) until we reach the proposed sample size. We will use the initial randomized list (which included determinations during the first 4 months of 2018) to select patients who meet both negative and positive PSA criteria and if it is necessary, we will continue to review analyses until the sample size is achieved. (Fig. 1)

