**Table 1 T1:**
[figure not shown]
Information to be extracted from the medical history.

We will follow both cohorts (positive and negative PSA results) for 2 years by reviewing their medical records (every 3 months for patients with a positive PSA result and annually for patients with a negative result). The following variables will be recorded: diagnostic interventions (digital rectal exam, biopsy, PSA determination, imaging tests), clinical interventions (medical consultations) and therapeutic interventions (radiotherapy, surgery, chemotherapy, hormonal treatment) during follow-up, collecting for each intervention the date and result obtained; and cancer diagnosis (date and cancer type).

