### Outcomes

3.4

The study outcomes associated with specific objective 1 are:

1.The effect size of the associations between clinical and analytical factors and false positive result in the determination of serum PSA levels (defined as positive result: if the total PSA value is >10 μg/L or a total PSA between 4 and 10 μg/L if the value of the free PSA/total PSA fraction is <25% in at least in 2 determinations and the result of digital rectal examination(s) and/or subsequent biopsy or biopsies are negative, according to the latest recommendations of the European Association of Urology^[20]^).2.The effect size of the associations between clinical and analytical factors and false negative result in the determination of serum PSA levels (defined as false negative result: if the PSA value is negative, and the patient is diagnosed with PCa in the subsequent follow-up, 2 years, according to the latest recommendations of the European Association of Urology^[20]^).

While for specific objective 2 the study outcomes are as follows:

1.Frequency of patients with appropriate diagnostic interventions performed in those with a positive serum PSA value according to “EAU - ESTRO - ESUR - SIOG Guidelines on Prostate Cancer”.^[32]^ Which is defined as strategies that satisfies or not satisfies EAU recommendations with regard to the following issues (Recommendations for clinical diagnosis of prostate cancer and Recommendations for repeat-biopsy imaging)2.Frequency of prostate cancer patients with an appropriate therapeutic interventions according to “EAU - ESTRO - ESUR - SIOG Guidelines on Prostate Cancer”.^[32]^ Which is defined according to the EAU recommendations with regard to the number and type of therapeutic interventions carried out after prostate cancer diagnosis. The following information will be considered: surgical treatments, radiotherapeutic treatments, active therapeutic options outside surgery and radiotherapy.

Two researchers will independently analyze diagnostic, and therapeutic interventions performed after a positive PSA value the follow-up deadline, and their adaptation to the latest available recommendations.^[32]^ Each patient will be classified as “Appropriate according to guideline”, “more intensive than guideline” or “less intensive than guideline”.

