## Discussion

4

The present study will allow showing the proportion of false positives and negatives obtained in clinical practice. We will provide knowledge on the modification of PSA levels according to relevant clinical variables and the association of the value of PSA with diagnostic and clinical interventions. This may support the basis of new recommendations about relevant aspects of urological clinical such as: the predictive value of clinical/diagnostic interventions associated with PSA value and patient management, depending on patient characteristics and the value of PSA and other clinical/diagnostic interventions obtained.

This study is not without limitations. First, we will retrieve the data from medical files, thus the quality of the data collected is highly dependent on the quality of the information recorded in the files. Thankfully, a recent update to an electronic system in the participating hospitals makes is possible for us to access data from different sources (primary, specialized and hospital care) and this is likely to improve data completeness and quality for the study. In addition, the UAE recommends using the Geriatric-8 and mini-COG tools for health status screening.^[32]^ We will not have all the information to apply them and instead we use life expectancy together with the Charlson Comorbidity Index.

Second, some degree of loss to follow-up is unavoidable and this may impact study results. Periodic review of the medical records should minimize this limitation. Finally, due to the nature of the study, we will not be able to evaluate the presence of overdiagnosis and overtreatment. We plan to evaluate the stage and characteristics of the PSA-detected prostate tumors, which may give us an indication of the potential for overdiagnosis, but given that the study is carried out in a routine clinical population, it is not possible to include a control population.

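### Time until cancer is ruled out is summarised only in men who reach that point within follow-up, so it understates the wait after a positive PSA

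*Protocol article*

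**What the plan says.** Section 3.5 (Statistical analysis), under specific objective 1, fixes both the group and the summary: for men with a false positive test it plans to give the "time from a positive PSA result until PCa is ruled out using mean, standard deviation or median and interquartile ranges". It is to be given for the whole population and for relevant subgroups.

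Section 3.4 (Outcomes) defines a false positive as a positive PSA followed by a negative digital rectal examination and/or biopsy. A man therefore belongs to the group only after a negative result has been recorded.

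Section 3.3 (Data collection procedure) bounds the time in which that can happen. Both cohorts are followed "for 2 years by reviewing their medical records (every 3 months for patients with a positive PSA result and annually for patients with a negative" one. Dates and findings of each diagnostic intervention are collected, as is the date of any cancer diagnosis.

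Section 3.2.2 adds an allowance to the sample size: "Taking into account a 20% possible loss during follow-up". The Discussion accepts that "some degree of loss to follow-up is unavoidable and this may impact study results". Section 3.5 ends with a general promise to use missing-data methods where needed.

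**The concern.** The summary is restricted to men who have already reached the event being timed. A PSA-positive man without cancer whose work-up runs past 24 months never becomes a false positive in the data. Nor does one who leaves or dies before a negative examination or biopsy. The longest waits are the ones removed, so the reported mean or median comes out too short as a statement about waiting after a positive test.

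The abstract says that the study will quantify potential harm, and time spent with an unresolved positive test is one part of that. The subgroup figures are exposed as well. A subgroup with slower work-up or more loss is trimmed harder, so differences between subgroups can shrink or be distorted.

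**Working it through.** **The plan's own figures.** The article gives no expected time to rule-out, so there is none to reproduce. The related figure is the loss allowance: 457/(1 − 0.20) = 571.25, stated as 572, and 865/(1 − 0.20) = 1081.25, stated as 1081. Both reproduce. At 20% loss, about 0.20 × 1081 = 216 PSA-positive men could leave early. Enlarging the sample restores precision but does not bring these men into the time summary.

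**Who enters the summary.**

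| PSA-positive man | In the false positive group? | Contributes a time? |
|---|---|---|
| Negative examination or biopsy by 24 months | Yes | Yes |
| Cancer diagnosed | No | No, correctly |
| Work-up still open at 24 months | No | No |
| Lost or dead before a result | No | No |

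The last two rows are the problem.

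**Size, without loss.** Inputs: the 24-month cut-off (section 3.3) and an assumed exponential time to rule-out with true median m among men without cancer. The values of m are assumptions.

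- Resolved by 24 months: F(24) = 1 − 2^(−24/m).
- The median t among resolved men solves F(t) = F(24)/2, so t = −m × log2(1 − F(24)/2).
- For m = 12: F(24) = 1 − 2^(−2) = 0.75; t = −12 × log2(0.625) = 8.1 months.

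| True median (months) | Unresolved at 24 months | Median in resolved men (months) |
|---|---|---|
| 3 | 0.4% | 3.0 |
| 6 | 6.3% | 5.5 |
| 12 | 25.0% | 8.1 |
| 18 | 39.7% | 9.3 |

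**Size, with loss.** Same model, simulated with 1,000,000 men per row; 20% are lost at a time uniform over the 24 months and independent of resolution.

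| True median | True mean | Resolved | Median in resolved | Mean in resolved | Kaplan-Meier median |
|---|---|---|---|---|---|
| 3 | 4.3 | 96% | 2.9 | 4.1 | 3.0 |
| 6 | 8.7 | 88% | 5.2 | 6.8 | 6.0 |
| 12 | 17.3 | 69% | 7.6 | 8.9 | 12.0 |
| 18 | 26.0 | 55% | 8.7 | 9.7 | 18.0 |

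The illustration holds only men without cancer and has no deaths, so Kaplan-Meier is the right comparator here. It recovers the true medians from the same data.

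**Subgroups.** Without loss, two subgroups with true medians of 6 and 12 months read 5.48 and 8.14. The true gap of 6 months appears as 8.14 − 5.48 = 2.66 months, and the true ratio of 2.0 as 8.14/5.48 = 1.49.

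**The case against.** Four points can fairly be made for the plan.

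1. Every man classified as false positive has a rule-out date, so nothing is censored inside the group. The summary is correct for the group it names. This stands, and it is why the fault is selection on resolution rather than mishandled censoring. It does not help a reader who takes the figure as the wait after a positive PSA.
2. Time to rule-out is not among the outcomes in section 3.4. It appears once, as something that will also be described. This stands. A reader might take it for the study's main measure of burden, but the article gives it no such status.
3. The speed of work-up is unknown, and if it is fast the error is trivial (3.0 months reads 3.0, or 2.9 with loss). The 20% is described as possible, and follow-up uses linked primary, specialised and hospital records. This stands as a limit on the size.
4. Section 3.5 promises missing-data methods. This does not answer the point: unresolved men have no missing value within the false positive group, because they are outside it.

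A reader might also infer that the 2-year false-negative results are biased, since the outcome is binary ("if the PSA value is negative, and the patient is diagnosed with PCa in the subsequent follow-up, 2 years") and "we will calculate prevalence ratios and their 95% confidence interval with log-binomial regression". The documents do not support that. A fixed 2-year risk in a binary model is legitimate when status at 2 years is known. In a check with a true risk of 5% and 20% independent loss, men with complete follow-up gave 5.0%. A man who dies without a cancer diagnosis is a non-event both in the binary coding and under competing risks. The article does not say that lost men count as non-cases. How they are handled is missing-data detail that a fuller document may settle.

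**Conclusion.** The point holds for the time summary only. Section 3.5 fixes a group and an estimator that together exclude PSA-positive men still unresolved at 24 months, lost or dead, so the figure understates how long men wait after a positive test. The 24-month cut-off can only push it downward. Early loss adds to this if loss is independent of resolution; with dependent loss, the direction of that part is not settled.

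The size runs from negligible when the true median is 3 months to about a third too short at 12 months (8.1 against 12, without loss) and about half at 18 months (9.3 against 18). These figures rest on exponential times and assumed medians; only the 24-month limit and the 20% allowance come from the article. The affected statistic is an additional descriptive one. The false-negative proportion and prevalence ratios are not shown to be at fault.

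**What to change.** In section 3.5, start the clock at the positive PSA for all PSA-positive men. Estimate the cumulative incidence of cancer being ruled out over 24 months, with cancer diagnosis and death as competing events and censoring at the last record. Report it overall and by subgroup, and state the proportion still unresolved at 24 months.

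This describes all positive men, including those who prove to have cancer, so the curve levels off below 100% and may never reach 50%. It is best read at fixed times rather than through a median.

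If the mean or median in false positive men is kept, label it as conditional on resolution within 2 years and place it beside the curve.

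The cost is a change of analysis wording and slightly more analysis work. Dates of interventions and of cancer diagnosis are already collected. Date of death and date of last record would have to be extracted from the same records if Table 1 does not already include them. No change to recruitment or sample size is needed.

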## Abstract

**Introduction::**

Prostate-specific antigen (PSA) is the main tool for early detection, risk stratification and monitoring of prostate cancer (PCa). However, there are controversies about the use of PSA as a population screening test because of the high potential for overdiagnosis and overtreatment associated. The net benefit of screening is unclear and according to the available recommendations, it should be offered to well-informed men with an adequate health status and a life-expectancy of at least 10 years or to men at elevated risk of having PCa. In addition, the factors that influence test results are unclear, as is impact of false positive or negative results on patient health.

Our objective is to assess the clinical and analytical factors associated with the presence of false positive and false negative results and the diagnostic/therapeutic process followed by these patients.

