Furthermore, several clinical or sociodemographic factors may influence PSA levels, how results interpreted, and hence false positives or negatives in a PSA test. Previous studies have evaluated variations of PSA levels according to demographic parameters such as age,^[21]^ although the clinical significance of these variations has not been evaluated in clinical practice. Regarding race, there are studies that showed variations in PSA level^[22]^ while others found no differences.^[23]^ Some studies suggest that clinical factors such as diabetes^[24]^ and obesity^[25]^ are associated with a lower likelihood of having a positive PSA test. Similarly, treatments like statins,^[26]^ metformin^[27]^ or treatment for benign prostatic hypertrophy^[28]^ can also affect PSA results. Many of these factors are highly prevalent in the target population for PCa screening.

To date, there are no studies evaluating the impact of these factors on a false positive or negative PSA result performed in general practice. The majority of studies have been carried out as part of clinical trials that evaluate the usefulness of PSA as a screening test, where the population is different from that with a PSA determination in routine clinical practice. Clinical trials tend to include healthier and younger patients and often represent a highly selected patient population.^[29]^ The impact of PSA determination on the patient's clinical management and evolution has not been evaluated either. This includes possible adverse effects related to the diagnostic process (biopsy, surgery and treatment), and the relationship between PSA determination and other factors that are considered when making the decision to request a biopsy such as patient comorbidity, Charlson index and PSA density, index or velocity.

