### Specific objectives

2.2

1.To analyze the clinical and analytical factors associated with the presence of false positive and false negative results in PSA determinations in patients undergoing opportunistic screening or with symptoms suggestive of disease.2.To evaluate the patient's clinical outcome, and any diagnostic and/or clinical and/or therapeutic interventions over a 2-year period after PSA testing. Furthermore, we will study whether this management is appropriate to the recommendations of the European Association of Urology.

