### Data collection procedure

3.3

Both hospitals have digital medical records which will be used to collect individual patient data. Furthermore, we will use the variables collected for the cross-sectional study as baseline data. These variables include demographic and clinical characteristics (patient who has the PSA determination as part of opportunistic screening or due to the presence of symptoms suggestive of disease), setting (primary care or clinical service), toxic habits, previous history of cancer, family history, present pharmacological treatment, PSA tests carried out in the last 12 months and PSA value, anthropometric measures and other comorbidities (Table 1).

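### Whether a PSA-positive man is verified depends on comorbidity, which can also be tested as a factor for a false positive, so the prevalence ratios can partly reflect who was biopsied

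*Protocol article*

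**What the plan says.** All references are to the protocol article.

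- **Source of verification (section 3.3).** "We will follow both cohorts (positive and negative PSA results) for 2 years by reviewing their medical records". The study is observational and requires no work-up of its own; biopsy and rectal examination results exist only where routine care ordered them.
- **What drives biopsy (section 1).** The Introduction refers to "other factors that are considered when making the decision to request a biopsy such as patient comorbidity, Charlson index and PSA density, index or velocity".
- **Candidate factors (sections 2.2 and 3.3).** Specific objective 1 is "To analyze the clinical and analytical factors associated with the presence of false positive and false negative results in PSA determinations". The baseline data include "PSA tests carried out in the last 12 months and PSA value, anthropometric measures and other comorbidities". The Discussion adds, on health status, that "we use life expectancy together with the Charlson Comorbidity Index".
- **Outcome (section 3.4).** A false positive is a positive PSA where "the result of digital rectal examination(s) and/or subsequent biopsy or biopsies are negative". Men with neither test are not mentioned.
- **Analysis (section 3.5).** The measure is the prevalence ratio with its 95% interval, from log-binomial regression: "In order to analyze clinical and analytical factors associated with the presence of false positive and false negative results in PSA determinations, we will calculate" these. A general sentence foresees methods for missing data or data of uncertain origin where needed. It does not mention disease status that was never established.

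**The concern.** Comorbidity can act at two points. It helps decide whether a PSA-positive man is biopsied, and it can be an explanatory variable for an outcome that depends on whether he was biopsied. A factor with no bearing on PSA accuracy can then show a prevalence ratio different from 1.

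The direction depends on a choice that sections 3.4 and 3.5 leave open:

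- If only biopsied men are analysed, and comorbid men are biopsied mainly when suspicion is high, comorbidity looks protective in a crude comparison.
- If unbiopsied men with a normal examination count as false positives, missed cancers accumulate among comorbid men and comorbidity looks harmful.
- If unbiopsied men stay in the denominator as not false positive, comorbidity looks strongly protective.

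The factor associations are themselves the objective 1 outcomes. The Discussion says the work may support new recommendations, and section 3.7 plans a report to technology assessment agencies. An effect of the care pathway could be read as a property of the test.

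**Working it through.** The plan states no verification rate and no expected prevalence ratio, so there is no plan figure to reproduce. The only anchor is the cancer fraction among PSA-positive men that follows from section 3.2.2.

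**Step 1. Implied cancer fraction.** With sensitivity 21%, specificity 91% and prevalence 5%:

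0.21 × 0.05 / (0.21 × 0.05 + 0.09 × 0.95) = 0.0105 / 0.0960 = 10.9%.

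Section 3.2.2 calls 5% a lower limit for prevalence, so a higher fraction is shown too; 35% is an assumption.

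**Step 2. Assumptions for the illustration (none is in the document).**

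- 40% of men are under high suspicion, in both comorbidity groups.
- Biopsy rates at high/low suspicion are 85%/60% in fit men and 50%/10% in comorbid men.
- Biopsy is always right. In unbiopsied men, examination finds 20% of cancers and is normal in every man without cancer.
- The cancer fraction is the same in both groups, so the true ratio is 1.00.
- At 35% overall, cancer is 60% at high and 18.3% at low suspicion (0.4 × 60 + 0.6 × 18.3 = 35). At 10.9% both are scaled by 10.94/35, to 18.75% and 5.73%.

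**Step 3. Biopsied share.** Comorbid: 0.4 × 0.50 + 0.6 × 0.10 = 0.26. Fit: 0.4 × 0.85 + 0.6 × 0.60 = 0.70.

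**Step 4. Cancers found at biopsy, as a share of all men in the group.**

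- At 35%: comorbid 0.20 × 0.60 + 0.06 × 0.183 = 0.131; fit 0.34 × 0.60 + 0.36 × 0.183 = 0.270.
- At 10.9%: comorbid 0.20 × 0.1875 + 0.06 × 0.0573 = 0.0409; fit 0.34 × 0.1875 + 0.36 × 0.0573 = 0.0844.

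**Step 5. False-positive proportions.**

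- Biopsied only, crude: 1 − found / biopsied.
- Unbiopsied kept: 1 − [found + 0.2 × (cancer − found)].

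| Cancer | Reading | Comorbid | Fit | Ratio |
|---|---|---|---|---|
| 10.9% | biopsied only | 84.3% | 87.9% | 0.96 |
| 10.9% | unbiopsied kept | 94.5% | 91.1% | 1.04 |
| 35% | biopsied only | 49.6% | 61.4% | 0.81 |
| 35% | unbiopsied kept | 82.5% | 71.4% | 1.16 |

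**Step 6. Unbiopsied men counted as not false positive.** If biopsy depends on comorbidity alone, the ratio is b₁(1 − c) / [b₀(1 − c)] = b₁/b₀, whatever the cancer fraction c. With 80% of fit men biopsied against 60%, 40% or 20% of comorbid men, it is 0.75, 0.50 or 0.25.

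**Step 7. When there is no bias.** Among biopsied men at the same suspicion level, both groups have the same false-positive proportion (at 35% cancer and high suspicion, 1 − 0.60 = 40% in each), so the ratio is 1.00. The same holds if biopsy depends on comorbidity alone and only biopsied men are analysed.

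**Step 8. Other inputs for the kept reading.** With biopsy rates as in step 6 and an examination sensitivity s of 30% to 50%, the false-positive proportion is 1 − c[b + (1 − b)s]. The ratio then runs from 1.01 to 1.05 at 10.9% cancer and from 1.06 to 1.26 at 40%.

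**The case against.** The strongest reply has four parts.

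1. **The article condenses a fuller plan, and some provisions are relevant.** An unverified status is a kind of missing outcome, and section 3.5 promises missing-data methods. Objective 2 also estimates the probability of a diagnostic intervention by patient variables, which would show who is worked up. This stands in part. But the article itself fixes the outcome in 3.4 and the estimator in 3.5, and nothing links the objective 2 analysis to objective 1. Reviewing records cannot recover a biopsy that was not done. The limitations in the Discussion cover record quality, loss to follow-up and overdiagnosis, not selective verification.

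2. **The biopsied-only bias is a crude one.** It vanishes within suspicion strata (step 7), so a log-binomial model holding the right variables would remove it. This is correct, and it is why adjustment is as acceptable a remedy as weighting. The plan does not, however, restrict the analysis to biopsied men.

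3. **The size is assumed, and small on the protocol's own inputs.** This stands: at 10.9% the table's ratios are about 4% from 1. A reader might infer from the 35% case that a null factor would be reported as significant. That does not follow. The interval around 0.81 is about 0.66 to 0.99 only if 864 men split equally by comorbidity. With 40% comorbid it is 0.65 to 1.01, and with 25% it is 0.61 to 1.06. At 10.9% cancer and equal groups it is 0.88 to 1.05 around 0.96.

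4. **The overlap is narrower than it may look.** A reader might infer that PSA density and velocity are also tested factors. The text does not name them as such; prior PSA values are collected, and Table 1 is not shown. Charlson appears as a stand-in for health-status tools. Comorbidity alone carries the point.

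The kept reading also rests on the either/or wording in 3.4, so this concern is not fully separate from the choice of reference test.

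**Conclusion.** The concern holds as a possibility that the plan leaves open, not as a demonstrated bias. Each link is in the article: verification through routine care, comorbidity in the biopsy decision, comorbidity among the baseline factors, and an outcome that an examination alone can settle, with no class for men without either test.

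The size cannot be derived from the document. With no true effect and the assumed biopsy rates, the ratio is 0.96 or 1.04 at 10.9% cancer and 0.81 or 1.16 at an assumed 35%, depending on how unbiopsied men are handled. It is well below 1 if they are counted as not false positive. Biopsied-only analysis is unbiased if the model contains the variables that determine biopsy.

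It would go too far to say that the sign of the study's main association is at risk: the article designates no main association among the factors.

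**What to change.** 1. At 2 years, classify every PSA-positive man as cancer, biopsy-verified no cancer, or unverified, with examination-only men in the last class. Report the three classes by each factor.
2. Estimate the false-positive associations in biopsy-verified men. Either adjust for recorded predictors of verification or weight by the inverse probability of verification. Candidate predictors are age, Charlson index, indication, PSA level and history, free/total fraction, rectal examination result and centre.
3. Add bounds that treat unverified men as all having cancer and as all cancer-free.
4. List selective verification among the limitations in the Discussion.

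This is extra analysis on data extracted from the records, with no new patients or procedures and no change to care. The price is wider intervals and reliance on the recorded variables to explain verification; the bounds show how much rests on that.
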